## Abstract

**Methods::**

This study is a randomized, multicenter, open-label, investigator-initiated phase 3 study. Patients with adjuvant/neoadjuvant or first-line palliative chemotherapy comprising intensively myelosuppressive agents on day 1 (mFOLFIRINOX, ECb, EP, FOLFIRI, and FOLFOX) are enrolled. The patients are assigned to the same-day arm or the next-day arm in a 1:1 ratio. The randomizations are stratified according to number of patient CIN risk factors (1 vs ≥2), chemotherapy setting (perioperative vs palliative), and interval (2-week vs 3-week). In the same-day arm, pegteograstim 6 mg is subcutaneously injected within 4 hours after completion of chemotherapy. In the next-day arm, pegetograstim is injected at 24 to 36 hours post-chemotherapy. A complete blood count test is performed daily from day 5 to 9 during the cycle 1. The primary endpoint is duration of Gr4 CIN (cycle 1), and secondary endpoints include incidence of Gr 3 to 4 CIN (cycle 1), severity of CIN (cycle 1), time to recovery absolute neutrophil count 1000/μL (cycle 1), incidence of febrile neutropenia, incidence of CIN-related dose delay, and dose intensity. In order to verify non-inferiority of 0.6 days, we estimated a significance level of 5%, power of 80%, and drop-out rate of 15%. This results in the need for a total of 160 patients, 80 in each group.

## 1. Introduction

### 1.1. Background

Chemotherapy-induced neutropenia (CIN) is one of representative adverse events (AEs) of cytotoxic chemotherapy that^[1]^ increases risk of febrile neutropenia (FN) and related mortality,^[2]^ reduces the effects of chemotherapy due to dose-limiting toxicity, and^[3]^ increases costs related to treatment of FN.^[4]^ Since CIN occurs most frequently during the first cycle of chemotherapy and adversely affects the clinical outcome, primary prophylaxis using granulocyte-colony-stimulating factor (GCSF) is recommended at the beginning of chemotherapy cycle 1 in patients with high-risk or moderate risk with risk factors.^[1]^

Pegylated granulocyte-colony-stimulating factor (peg-GCSF) was developed to increase the half-life to 46 to 72 hours by attaching polyethylene glycol to filgrastim so that only 1 administration per cycle is necessary to prevent CIN. A single injection of peg-GCSF showed an equivalent effect to daily filgrastim therapy in a comparative study.^[5]^ Based on the mechanism of action of peg-GCSF and results of prior prospective and meta-analysis studies,^[3,6]^ administration of peg-GCSF 24 to 72 hours after completion of chemotherapy is recommended.^[1]^ Patients in which the next-day method (administration after 24 hours post-chemotherapy) was implemented had fewer days in Grade (Gr) 4 neutropenia than the same-day method (administration within 4 hours post-chemotherapy). CIN was also less severe in the next-day group.

However, approximately 13% of patients receive same-day peg-GCSF probably due to the inconvenience of providing an additional hospitalization or hospital visit for administration of the peg-GCSF.^[7]^ In addition, in some retrospective studies or subgroup analyses, the same-day method was comparable or superior to the next-day method in preventing CIN in multi-day (3 to 5 days) regimens in which myelosuppressive agent administration was concentrated on day 1.^[3,8]^ Therefore, there is a need to reevaluate the efficacy of the same-day method in such cases.

Pegteograstim is a new formulation of peg-GCSF, that was developed by Green Cross Corporation in Korea. Pegteograstim was compared with the pegfilgrastim in a 2016 phase II/III study. There was no significant difference in Gr4 CIN duration (pegteograstim 1.97 days, pegfilgrastim 1.54 days, *P* = .33), and pegteograstim showed a significantly shorter CIN recovery time (pegteograstim 8.85 days, pegfilgrastim 9.83 days, *P* < .001).^[9]^

### 1.2. Study aims

Our study aim is to test the hypothesis that same-day administration of pegteograstim is non-inferior to next-day administration in controlling CIN Gr4 duration during first cycle in patients treated with chemotherapy regimens that contain intensively myelosuppressive agents on day 1.

## 2. Methods

### 2.1. Study design

This study is a randomized, multicenter, parallel, open-label, phase III study. This study is designed to test the non-inferiority of same-day to next-day administration of pegteograstim (Fig. 1).

**Figure 1. F1:**
[figure not shown]
Study flowchart.

### 2.2. Study registration

This study trial has been registered on the Clinical Research Information Service (http://cris.nih.go.kr) with the ID No. KCT0007694 (Release date: September 15, 2022).

### 2.3. Participants

Patients with adjuvant/neoadjuvant or first-line palliative chemotherapy with regimen containing an intensively myleosuppressive agent on day 1 are enrolled.

Enrollment criteria are: Patients with histologically confirmed malignancy who are scheduled for adjuvant/neoadjuvnat or first-line palliative chemotherapy with multi-day combination regimens. These regimens include mFOLFIRINOX for Pancreatic cancer, ECb and EP for Small cell carcinoma, Neuroendocrine carcinoma, and FOLFOX and FOLFIRI for colorectal cancer. Detailed contents of these regimen are described in Table 1. The patients receiving FOLFOX and FOLFIRI combination therapies with targeted agents such as cetuximab or bevacizumab are also included, and those receiving atezolizumab in addition to the ECb and EP regimens for small cell lung carcinoma are also eligible; Patients with 1 or more risk factors for CIN: 65 years of age or older, previous history of chemotherapy or radiation therapy, recent surgery and open wounds, liver dysfunction with total bilirubin > 2.0 mg/dL, renal dysfunction with creatinine clearance < 50 mL/minutes. An exception is that patients on the mFOLFIRINOX regimen can be enrolled without CIN risk factors due to the high-risk for CIN of this regimen; Patients who are scheduled to receive 100% dose of chemotherapy; Patients between the ages of 19 and 75; Patients with Eastern Cooperative Oncology Group performance status 0 to 1; Patients with adequate bone marrow function for chemotherapy [absolute neutrophil count (ANC) ≥ 1500/μL], (platelets ≥ 100,000/μL, and hemoglobin ≥ 9.0 g/L), adequate renal function (creatinine clearance ≥ 40 mL/minutes), adequate liver function [total bilirubin in the blood < 1.5 × upper limit normal (ULN), alanine aminotransferase or aspartate aminotransferase  < 3.0 × ULN. The alanine aminotransferase or aspartate aminotransferase value must be ≤ 5.0 × ULN in patients with documented disease metastases to the liver); Patients who agreed to participate in the study.

**Table 1 T1:** Chemotherapy regimens.

Cancer type	Regimen		Day
Pancreatic cancer	mFOLFIRINOX		Every 2 wk
	5-FU	1200 mg/m^2^ IV continuous infusion	d 1–2
	Oxaliplatin	85 mg/m^2^ IV	d 1
	Irinotecan	150 mg/m2 IV	d 1
Small cell carcinoma, Neuroendocrine carcinoma	EP*		Every 3 wk
	Etoposide	100 mg/m^2^ IV	d 1–3
	Cisplatin	70 mg/m^2^ IV	d 1
Small cell carcinoma, neuroendocrine carcinoma	ECb*		Every 3 wk
	Etoposide	100 mg/m^2^ IV	d 1–3
	Carboplatin	AUC 6.0 mg/mL IV	d 1
Colorectal cancer	FOLFOX†		Every 2 wk
	5-FU	3000 mg/m^2^ IV continuous infusion	d 1–2
	Oxaliplatin	85 mg/m^2^ IV	d 1
	Leucovorin	400 mg/m2 IV	d 1
Colorectal cancer	FOLFIRI†		Every 2 wk
	5-FU	3000 mg/m^2^ IV continuous infusion	d 1–3
	Leucovorin	400 mg/m2 IV	d 1
	Irinotecan	180 mg/m2 d 1	d 1

* Combination therapies with atezolizumab are also included.

† Combination therapies with targeted agents such as cetuximab or bevacizumab are also included.

The exclusion criteria are: Patients aged 76 years or older, Patients unable to receive 100% dose intensity in cycle 1; Patients who underwent radiation therapy within 1 month before starting treatment; Patient with other serious diseases or medical conditions; Pregnant or lactating women or those of childbearing age who do not consider contraception.

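### The haemoglobin entry limit in section 2.3 is written as 9.0 g/L, a value and unit that cannot both be intended; as written it excludes nobody

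*Protocol article*

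**What the plan says.** The enrollment criteria in section 2.3 (Participants) require marrow reserve to be shown by three values. The first is the neutrophil count: "Patients with adequate bone marrow function for chemotherapy [absolute neutrophil count (ANC) ≥ 1500/μL". The other two follow directly: "platelets ≥ 100,000/μL, and hemoglobin ≥ 9.0 g/L".

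The same list limits the population to "Patients with Eastern Cooperative Oncology Group performance status 0 to 1" and to patients planned for the full chemotherapy dose. The exclusion criteria, after Table 1 in the same section, contain no haemoglobin value. The nearest entry is the general "Patient with other serious diseases or medical conditions". Haemoglobin appears nowhere else in the article, so no second statement of the limit or its unit exists to compare with this one.

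**The concern.** An entry limit works only if some plausible candidates fall on the wrong side of it. A haemoglobin floor of 9.0 g/L lies far below anything a candidate for this trial could have. Applied literally, the rule passes every patient, including a severely anaemic one.

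What is at stake is safety screening and the ability to audit eligibility. The limit is one of three numerical conditions meant to show marrow reserve before full-dose myelosuppressive treatment. If it is ineffective as written, the text has no working numerical floor for haemoglobin. Anyone who applies a sensible limit instead is applying a rule that the article does not state.

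**Working it through.** **Inputs, all from section 2.3**

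- Haemoglobin limit as written: at least 9.0 g/L.
- The other two marrow limits: neutrophils at least 1500/μL and platelets at least 100,000/μL.
- Population: performance status 0 to 1, scheduled for the full dose.

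**Step 1: convert the written limit.** There are 10 dL in 1 L, so a value in g/dL is the value in g/L divided by 10.

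9.0 g/L ÷ 10 = 0.9 g/dL.

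**Step 2: see whom it excludes.** Take a severely anaemic patient at 6 g/dL, an illustrative value that is not in the article.

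6 g/dL × 10 = 60 g/L, and 60 ÷ 9.0 = 6.7.

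This patient clears the written limit more than six times over. For a candidate to fail, haemoglobin would have to be below 0.9 g/dL, which is not credible in the population described. The criterion therefore removes nobody.

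**Step 3: size the discrepancy under the natural reading.** Assume that the number 9.0 was intended and the unit should have been g/dL.

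9.0 g/dL × 10 = 90 g/L, and 90 ÷ 9.0 = 10.

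The factor of 10 depends on that assumption. Step 2 does not.

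**Step 4: rule out an artefact of text extraction.** The bilirubin risk factor in the same list is printed in mg/dL with the unit intact. The loss of a single letter from the haemoglobin unit is therefore not explained by how the text was read.

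**Step 5: see whether the design figures depend on it.** Section 2.10 uses a margin of 0.6 days, a standard deviation of 1.4 days, 5% significance and 80% power. With the 5% taken as one-sided and a true difference of zero:

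n per arm = 2 × (1.645 + 0.842)² × 1.4² ÷ 0.6² = 67.3, rounded up to 68, or 136 in total.

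68 ÷ (1 − 0.15) = 80 per arm, or 160 in total.

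Both totals match section 2.10. No haemoglobin value enters the calculation, so correcting the limit changes neither.

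**The case against.** The strongest reply is that this is a self-evident slip. A clinician cannot be misled by a physiologically impossible limit in the way that a plausible wrong number could mislead, and most sites would probably read the unit as g/dL. The article also condenses a fuller protocol that was approved by a review committee and the ethics boards (section 2.12) and is not shown here. That document and the case report form may well be correct. Other filters remain too: performance status, the full-dose requirement and the general exclusion for serious conditions.

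Most of this stands, and it limits the weight of the point. It does not remove the error. The article states an operative entry criterion, and states it wrongly. The remaining filters carry no haemoglobin value and do not replace the limit.

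Three stronger readings are tempting but not supported:

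- **Sites are applying different limits, or an electronic check is passing everyone.** Section 2.12 mentions electronic case report forms, but nothing says that they contain an eligibility check, which unit it would use, or that sites screen from the article. Section 3 says that recruitment is under way, not that anyone was admitted under a wrong limit.
- **The neutropenia endpoint is affected.** Haemoglobin is not among the listed neutropenia risk factors, the stratification factors or the endpoints. The neutrophil limit, the one directly tied to the endpoint, carries no such fault. Any anaemic patient admitted would be randomized to either arm, so no bias between arms is evident.
- **The limit is simply ten times too low.** This presumes that the number is right and only the unit is wrong. It is the most natural reading, but the article does not confirm it.

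**Conclusion.** The point holds as a minor eligibility and safety error. As written, the haemoglobin limit equals 0.9 g/dL and one of the three marrow-function criteria has no screening effect. That conclusion rests on a unit conversion and on one assumption: that no performance status 0 to 1 candidate for full-dose chemotherapy has a haemoglobin near that level.

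The intended value and unit cannot be settled from the article, and no limit is proposed here. Practical harm is possible only if the operational documents carry the same error, which is unknown. The primary comparison is not affected.

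**What to change.** 1. Check the intended haemoglobin value and unit against the full approved protocol.
2. Correct section 2.3 so that the two agree.
3. Confirm that the operational protocol and the eligibility form carry the correct unit.
4. Re-check enrolled patients against the confirmed limit only if step 3 finds the same error in those documents.

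Steps 1 to 3 amount to a correction of one unit or value and a brief look at the form, at negligible cost. Step 4 is conditional and would need only screening haemoglobin values. The sample size and the analysis do not change.

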### 2.4. Recruitment

We will recruit 160 participants scheduled to receive multi-agent chemotherapy regimens with intensively myleosuppressive agents on day 1 (mFOLFIRINOX, ECb, EP, FOLFOX, FOLFIRI) as an adjuvant/neoadjuvant or first-line palliative treatment in 5 Korean academic hospitals (Pusan national university yangsan hospital, Hanyang University Seoul Hospital, Dong-A University hospital, Haeundae Paik Hospital, Kosin University Gospel Hospital) (Fig. 1). The researcher explains the aim and the methods of the study to the participants and obtains informed consent from potential participants before the collection of medical information.

### 2.5. Intervention

For those in the same-day arm, pegteograstim 6mg is subcutaneously injected within 4 hours after completion of chemotherapy. Those in the next-day arm receive pegteograstim 6mg subcutaneously 24 to 36 hours after completion of chemotherapy.

### 2.6. Randomization and stratification

The patients are randomized 1:1 in a centralized block randomization manner to be allocated to either the same-day or the next-day arm. The randomization is stratified according to number of patient’s CIN risk factors (1 vs ≥ 2), chemotherapy setting (perioperative vs palliative), and interval of regimen (2-week vs 3-week). This clinical study is an open-label trial; both the investigator and the patient know which method is being administered.

### 2.7. Evaluation and outcome measure

During cycle 1, a complete blood count (CBC) test is performed every day from day 5 to 9. If the ANC rises for 2 consecutive days before day 9 and is over 1000/mm^3^, CBCs can be stopped. Conversely, if the ANC does not recover to 1000/mm^3^ or more until day 9, the daily CBC should be continued until the ANC recovers to 1000/mm^3^. From cycle 2 to 4, anticancer treatment is performed according to general practice; and neutropenic fever, dose of chemotherapy, and AEs are assessed.

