-Duration of Gr4 CIN (cycle 1): duration (in days) of ANC < 500/μL in the first chemotherapy cycle.-Incidence of Gr 3 to 4 CIN (cycle 1): subjects with ANC < 1000/μL in the first chemotherapy cycle.-Severity of CIN (cycle 1): minimum ANC level in the first chemotherapy cycle.-Time to ANC recovery (cycle 1): time (in days) from day 1 of chemotherapy to ANC > 1000/μL after the nadir in the first chemotherapy cycle.-FN incidence (cycle 1–4): development of FN until 28 days after the end of cycle 4. FN is defined as an oral temperature rise to 38.3°C or higher or a fever of 38.0°C or higher that lasts for 1 hour or more with an ANC <500/mm^3^ or with an ANC <1000/mm^3^ that is expected to decrease to <500/mm^3^ within 48 hours.-Incidence of CIN-related dose delay (cycle 1–4).-Relative dose intensity (RDI) (cycle 1–4): RDI is calculated by dividing the total dose of chemotherapy (mg/m^2^) by the total administration period, and the value was expressed as a percentage based on the full dose intensity (Table 1).-Pegteograstim-related AEs (cycle 1–4): the occurrence of bone pain and pneumonitis during cycles 1 to 4.

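### The cycle-1 CBC stopping rules do not require an observed fall in ANC, so some Gr4 days that the whole-cycle primary endpoint should count can go unobserved

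*Protocol article*

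**What the plan says.** Section 2.8 defines the primary endpoint as "duration (in days) of ANC < 500/μL in the first chemotherapy cycle", so the counting period is the entire cycle.

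Section 2.7 sets the schedule that feeds it: "a complete blood count (CBC) test is performed every day from day 5 to 9". Two rules modify the schedule.
- Early stop: "If the ANC rises for 2 consecutive days before day 9 and is over" 1000/mm³, testing may end.
- Extension: "if the ANC does not recover to 1000/mm^3^ or more until day 9, the daily CBC should be continued" until it does.

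Neither rule mentions a preceding fall or a nadir. By contrast, the time-to-recovery endpoint in Section 2.8 is explicitly counted from a point after the nadir.

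Section 2.11 makes the per-protocol set primary. One ground for exclusion is insufficient CBC testing, described both as under half of the tests and as testing on three days or fewer. A second limb covers testing that ends before ANC exceeds 500/μL.

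**The concern.** A rule that ends testing on a rising ANC is sound once the nadir has passed. It is not sound if the rise comes first.

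Table 1 gives chemotherapy through day 3 for EP, ECb and FOLFIRI. The same-day injection then falls on about day 3. For the other arm, "Those in the next-day arm receive pegteograstim 6mg subcutaneously 24 to 36 hours after completion of chemotherapy" puts it on about day 4 or 5. Testing opens on day 5, shortly after a drug given to raise neutrophils. An early rise before the nadir is therefore plausible, although the article gives no data on how often it occurs.

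The day-9 rule has a similar gap. A patient at, say, 1300/mm³ and falling on day 9 has reached the end of required testing.

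Gr4 days that are never observed cannot enter the primary endpoint. Minimum ANC and Gr 3–4 incidence rest on the same tests. In a non-inferiority trial, a similar loss in both arms moves the observed difference in the favourable direction.

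**Working it through.** **1. Who can be missed under Section 2.7**

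Tests start on day 5, so the first two rises that can be seen are day 5 to 6 and day 6 to 7.

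| Last test | Tests done | Share of the five scheduled |
|---|---|---|
| Day 7 | 3 | 3/5 = 60% |
| Day 8 | 4 | 4/5 = 80% |
| Day 9 | 5 | 100% |

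- Stop on day 7: ANC rose at every test, so no fall has been seen. Values of 4000, 6000 and 9000 (a made-up example) satisfy the rule.
- First qualifying on day 8: either ANC did not rise from day 5 to 6, or it was not yet over 1000/mm³ on day 7. Usually this means a fall or a low value was seen. The exception is a patient who could have stopped on day 7 but was tested once more.
- Day 9, below 1000/mm³: daily tests continue to recovery, so nothing is lost.
- Day 9, at or above 1000/mm³ and falling: no further test is required.

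**2. Does Section 2.11 catch them?**

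- A three-test stopper meets the three-days-or-fewer wording but not the under-half wording (60%). The criterion contradicts itself here, and on one reading it excludes a patient for a stop that Section 2.7 permits.
- A four-test stopper with a high ANC breaches neither limb and stays in the primary analysis.
- A day-9 faller has five tests and also stays in.

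**3. The plan's own sample size (Section 2.10)**

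Inputs: margin 0.6 days, SD 1.4 days, power 80%, significance level 5%, drop-out 15%, true difference 0. Sidedness is not stated.

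n per arm = 2 × (1.645 + 0.842)² × 1.4² / 0.6² ≈ 67.3, rounded up to 68; 68 / 0.85 = 80. This reproduces 136 and 160. One-sided 2.5% would give 86 per arm, so one-sided 5% is used below.

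**4. Effect of missed Gr4 days**

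SE = 1.4 × √(2/68) = 0.240. P(declare non-inferiority) = Φ((0.6 − observed difference)/SE − 1.645). The true difference (same-day minus next-day) is set at the margin, 0.6. The missed shares are assumptions, and the SD is held at 1.4.

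Same share missed in both arms:

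| Missed | Observed difference | False non-inferiority |
|---|---|---|
| 0% | 0.60 | 5.0% |
| 5% | 0.6 × 0.95 = 0.57 | 6.4% |
| 10% | 0.6 × 0.90 = 0.54 | 8.2% |

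Missed in one arm only, next-day mean 2.25 days (middle of the 2 to 2.5 days in Section 2.10), same-day mean 2.85:
- 10% in the same-day arm only: 0.9 × 2.85 − 2.25 = 0.315 days; 32%.
- 10% in the next-day arm only: 2.85 − 0.9 × 2.25 = 0.825 days; 0.5%.

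**The case against.** The strongest reply is that the gap is narrow. Everyone below 1000/mm³ on day 9, including every patient in Gr4 that day, is followed to recovery. Most day-8 stops follow an observed fall or low count. The three-test stopper may be excluded under Section 2.11 rather than analysed. Any later cycle-1 count below 500/μL already belongs to the endpoint as defined. All of this stands, and it limits the point to two subgroups. It does not remove the point: excluding a patient for a permitted stop is itself a conflict, and counting later values does not help if no later test is required.

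A reader might go further and infer several things that the document does not support.
- That Gr4 days after day 9 are generally lost. The extension rule prevents this for patients below 1000/mm³ on day 9.
- That unobserved days are scored as zero. The article gives no scoring rule, and any statistical analysis plan is not shown.
- That the arm difference must shrink. Injections are about a day apart while test days are fixed, so misses may differ by arm, and the one-arm examples run in opposite directions.
- That late nadirs are common because Section 1.1 reports a mean recovery time of 8.85 days where "pegteograstim showed a significantly shorter CIN recovery time". That is a mean from another study, and recovery follows the nadir, so it suggests that typical nadirs come before day 9.
- That a large share of all Gr4 days is missed. The document gives no share, and only two subgroups can contribute.

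**Conclusion.** The point holds in limited form. Followed exactly, Section 2.7 can leave Gr4 days unobserved in two groups: patients who stop on a rise with no fall seen, and patients at or above 1000/mm³ and still falling on day 9. Section 2.11 does not resolve either case and conflicts with Section 2.7 for a three-test stop.

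The size cannot be derived from the document. The rise in false non-inferiority to about 6.4% or 8.2% is an illustration. It assumes 5% or 10% of Gr4 days missed equally in both arms, a true difference of 0.6 days, 68 patients per arm, an unchanged SD of 1.4 and a one-sided 5% test. With unequal misses the direction is open. The case for acting is that the primary endpoint's ascertainment is left to chance in these groups and the repair is cheap.

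**What to change.** For endpoint ascertainment:
1. Allow early stopping only after an observed fall in ANC followed by rises on two consecutive days to over 1000/mm³. Otherwise complete the day 5–9 tests.
2. Continue daily CBCs past day 9 if ANC is still falling on day 9 (lower than on day 8), even at or above 1000/mm³, until it rises and is over 1000/mm³.
3. Rewrite the CBC criterion in Section 2.11 so that its two thresholds agree and a stop permitted by Section 2.7 is not a deviation.

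Cost: a minor amendment. The first change uses tests already scheduled; the second adds a few CBCs in patients still falling on day 9. Treatment is not affected.
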